## Abstract

**Introduction:**

Diabetes‐related foot ulceration (DFU) is a serious complication, serving as a leading cause of amputation, disability, hospitalisation and a significant contributor to healthcare costs. Deficiencies in vitamin C and other micronutrients are common in DFU. Emerging evidence suggests vitamin C supplementation may enhance wound healing; however, high‐quality randomised controlled trials are lacking. Therefore, the aim of this study is to investigate the efficacy of oral vitamin C supplementation (1 g/day) for 8 weeks on wound healing in people with DFU.

**Methods:**

This is a multi‐site, parallel group, randomised, placebo‐controlled, double‐blind trial. Eighty adults with DFU will be recruited and randomly assigned to either placebo or vitamin C supplementation (500 mg twice daily). Ulcer measurements will be obtained at baseline, 2, 4, 6 and 8 weeks with all other measures collected at baseline and 8 weeks. The primary outcome measure is the percentage reduction in ulcer size (ulcer volume in mm^3^) at 8 weeks, compared to baseline. Secondary outcomes are changes in plasma vitamin C, time to 50% ulcer healing, time to complete ulcer healing, rate of healing of ulcers and adverse events. Exploratory outcomes include changes to glycaemic status, blood lipids, blood pressure, peripheral arterial perfusion, mental health and well‐being, scurvy signs and symptoms and oxidative stress.

**Discussion:**

The findings from this research will provide high‐quality evidence on the efficacy of vitamin C for wound healing in people with DFU and help to inform clinical practice regarding vitamin C supplementation alongside current standard care to aid in the healing of DFUs.

**Trial Registration:**

Australian and New Zealand Clinical Trials Registry (ACTRN12624000675527). Universal Trial Number (UTN) U1111‐1308‐1050

## Introduction

1

Diabetes‐related foot disease (DFD) encompasses peripheral neuropathy, peripheral artery disease, ulceration, infection, gangrene, amputation and/or Charcot neuro‐osteoarthropathy [1]. DFD affects ∼200 million people worldwide and accounts for 2% of the global disease burden [2, 3], ranking it the 13th largest cause of the world's total disease burden [2, 3, 4, 5]. Diabetes‐related foot ulceration (DFU) is a common and serious complication of diabetes with a global prevalence of 6.3% [5]. Given that around 50% of DFUs will become infected [6, 7, 8] and 20% will result in lower limb amputation [7, 9], this makes DFU a leading cause of disability and hospitalisation [10, 11, 12, 13]. The condition significantly impacts a person's quality of life [2, 4, 14, 15] and places a substantial financial burden on healthcare systems and society [12, 16, 17, 18]. Therefore, new evidence‐based therapies to complement current standard care are urgently needed.

Vitamin C is a co‐factor required for collagen formation and thus plays an essential role in wound healing [19]. Vitamin C is also a potent antioxidant and supports various cellular functions of the immune system, both of which are important for healing and the prevention and management of infection, respectively [19]. In high‐income countries, the intake of vitamin C is generally thought to be more than adequate, and low or deficient levels of vitamin C are assumed to be rare [20]. However, recent evidence suggests there is a high prevalence of vitamin C deficiency in various adult hospitalised patient populations, some of which are likely to include people at risk of DFUs [20]. Furthermore, we [21] and others [22, 23] have reported that 50%–60% of patients with foot ulcers attending high‐risk foot services located in several major Australian cities are deplete or deficient in vitamin C.

Despite the strong association between low vitamin C levels and high levels of amputation in people with DFU [21, 23], there is a lack of high‐quality randomised controlled trials (RCTs) to support vitamin C supplementation for promoting the healing of DFUs. Indeed, a recent systematic review on the role of vitamin C supplementation in the management of DFUs found only three published human trials with the main conclusion being the need for additional human clinical trials on vitamin C supplementation in people with a DFU [24]. The most convincing evidence to date is by Gunton et al. [22] who found vitamin C supplementation improved foot ulcer healing by ∼50% in a cohort of 16 patients, of which half in the cohort had diabetes. Although this data is promising, it is limited by the small sample size.

The lack of high‐quality evidence in the field highlights the need for high‐quality RCTs in people with diabetes. Therefore, the aim of this study is to investigate the efficacy of oral vitamin C supplementation (1 g/day) for 8 weeks on wound healing in people with DFU. It is hypothesised that vitamin C supplementation (1 g/day) for 8 weeks will improve the percentage of ulcer healing in people with DFU.

## Materials and Methods

2

### Study Design

2.1

The FOOT ulcer treatment with vitamin C (FOOT‐C) study is a multi‐site, parallel group, randomised, placebo‐controlled, double‐blind trial. The study has been registered with the Australian and New Zealand Clinical Trials Registry (ACTRN12624000675527). This study protocol has been developed using the SPIRIT guidelines [25]. The associated checklist from the 2022 extension of the SPIRIT 2013 statement [26] is included as a supplemental file and the participant timeline is shown in Figure 1.

FIGURE 1SPIRIT diagram of enrolment, interventions, assessments and outcome measures in the FOOT‐C study. ALP: Alkaline phosphatase, ALT: Alanine aminotransferase, CES‐D: Centre for Epidemiologic Studies Depression, DDS17: Diabetes Distress Scale‐17, eGFR: estimated glomerular filtration rate, GGT: Gamma glutamyl transpeptidase, HbA1c: Haemoglobin A1c, SINBAD: Site, Ischaemia, Neuropathy, Bacterial Infection, and Depth, WIfI: Wound, Ischaemia, foot Infection.

**Figure d104e641:**
[figure not shown]

**Figure d104e643:**
[figure not shown]

### Intervention

2.2

Adults with a DFU will be recruited and undergo placebo or vitamin C supplementation in a double‐blind, randomised manner. The treatments will consist of oral ingestion of either vitamin C (500 mg ascorbic acid per capsule, two capsules per day; so, a total of 1 g/day) or placebo (microcrystalline cellulose capsule, two capsules per day) for 8 weeks. A placebo group as the comparator is considered the most rigorous test of treatment efficacy for evaluating a medical therapy in a double‐blind RCT [27]. Participants will be instructed to take one capsule in the morning and one capsule in the evening alongside meals. All outcome measures will be conducted at the beginning (baseline) and then at 8 weeks of treatment. Outcome measures for wound healing will also be recorded at fortnightly visits to the clinic during the 8‐week treatment period (Figure 1). The trial will conclude for each participant at 8 weeks or beforehand if the patient undergoes amputation or withdraws consent.

All participants will continue to receive usual standard of care throughout the trial. Standard care was defined according to the IWGDF Practical Guidelines (2023 update) [28] and comprised core evidence‐based prevention and management practices for DFD. This included routine risk‐based foot screening using structured assessments for neuropathy, peripheral artery disease, deformity, callus, pre‐ulcerative lesions, and any history of ulceration or amputation. Participants also received education on daily foot inspection, protective footwear use, foot hygiene, and prompt escalation for any foot concerns. Standard care additionally involved appropriate offloading and therapeutic footwear to reduce plantar pressure, as well as timely ulcer classification and management using best practice wound care and coordinated evaluation of infection or peripheral artery disease within a multidisciplinary model.

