### Adverse Events

2.9

Adverse events will be assessed and documented at every fortnightly visit for each participant by asking them whether they have experienced any unusual symptoms or medical problems since their previous study visit. As much detail as possible regarding the nature, severity and duration of the adverse event will be recorded. Bloating and diarrhoea are uncommon side effects of vitamin C supplementation and thus considered adverse reactions rather than adverse events, but they will still be documented and reported in any publication. Serious adverse events will be defined as events that result in death, are life‐threatening, require hospitalisation or the prolongation of an existing hospitalisation, or lead to persistent or significant disability or incapacity [55]. Participants will also be provided with 24‐h contact information for the study team and are encouraged to report any issues that may require medical attention.

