### Concomitant Care and Interventions

2.10

At every fortnightly visit following baseline, study staff will inquire about and record any changes to participants' medication/s, supplement usage or ulcer treatment. Participants will also be asked if they have seen a doctor or been hospitalised for any other medical reasons since their last visit.

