### Handling of Withdrawals

2.12

When scenarios of participant withdrawal occur for reasons such as voluntary withdrawal, medical withdrawal (including undergoing amputation), protocol violation and/or adverse events, the participant's data will be included in an ‘intention to treat’ analysis (as detailed below in 2.15). No data substitution will be applied for reporting of adverse events or intervention adherence.

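### Amputation ends trial participation, and no collection of serious adverse events or vital status is stated from then to week 8

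*Protocol article*

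**What the plan says.** The end-of-participation rule in section 2.2 (Intervention) reads: "The trial will conclude for each participant at 8 weeks or beforehand if the patient undergoes amputation or withdraws consent". Section 2.12 (Handling of Withdrawals) lists "medical withdrawal (including undergoing amputation") among the reasons for withdrawal. It keeps withdrawn participants in the intention-to-treat analysis and adds: "No data substitution will be applied for reporting of adverse events or intervention adherence".

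Safety data come by three stated routes:

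- Section 2.9: "Adverse events will be assessed and documented at every fortnightly visit for each participant".
- Section 2.9 also gives participants round-the-clock "contact information for the study team and are encouraged to report any issues that may require medical attention".
- Section 2.10, at the same fortnightly visits: "Participants will also be asked if they have seen a doctor or been hospitalised for any other medical reasons since their last visit".

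The serious-event definition in 2.9 covers fatal events and admissions: "Serious adverse events will be defined as events that result in death, are life‐threatening, require hospitalisation". The Methods part of the abstract closes its list of secondary outcomes with "rate of healing of ulcers and adverse events". Section 2.7.3 says that amputations are recorded and that these participants count as not healed.

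**The concern.** Read together, these sections stop the scheduled safety questions at an event that reflects the course of the ulcer. Take a participant who has an amputation at week 4 and is readmitted or dies at week 6. The later event lies inside the planned 8-week window and meets the definition in 2.9. By then, however, the trial has concluded for that person, and no stated process would pick the event up.

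Two things are at stake. First, a named secondary outcome is cut short in participants whose condition has just worsened. Second, the cut may depend on treatment. The introduction reports a strong association between low vitamin C and amputation. If supplementation lowers amputation, the arms are observed for different lengths of time, and a plain comparison of event counts is not like with like. Imputation will not close the gap: 2.15 provides it for missing outcomes, but 2.12 exempts adverse events. That exemption is sound, so the only remedy is to collect the data.

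**Working it through.** **Step 1. What each route yields after an amputation before week 8.**

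| Route | Tied to | After amputation, as written |
|---|---|---|
| Adverse event questions (2.9) | fortnightly visit | stop, because the trial has concluded for the participant (2.2) |
| Doctor and hospital look-back (2.10) | fortnightly visit | stop, for the same reason |
| 24-hour contact (2.9) | the participant's own report | not said to continue; cannot report the participant's own death |
| Amputation record (2.7.3) | the amputation | captures the amputation, not what follows |

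No section provides for serious events or vital status between amputation and week 8.

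**Step 2. The plan's own withdrawal figure.** Section 2.14 gives d = 0.80, two-sided α = 0.05 and 90% power, with 34 per group. A two-sample t-test with 34 per group has power 90.2%, so this reproduces. With 15% withdrawal, 68 / 0.85 = 80, which also reproduces. Expected withdrawals are 80 × 0.15 = 12.

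**Step 3. Planned observation.** 80 participants × 8 weeks = 640 participant-weeks, or 320 per arm at 1:1 allocation.

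**Step 4. Upper bound on lost time.** Suppose all 12 withdrawals end safety observation. Lost share = 12 × (8 − mean exit week) / 640. The exit week is an assumption.

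| Mean exit week | Lost participant-weeks | Share of 640 |
|---|---|---|
| 2 | 12 × 6 = 72 | 11.25% |
| 4 | 12 × 4 = 48 | 7.5% |
| 6 | 12 × 2 = 24 | 3.75% |

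This is a bound because the 12 include every kind of withdrawal. It takes amputations to be within the 15%, as 2.12 suggests. The amputation share cannot be separated, because the article gives no amputation rate for this population over 8 weeks.

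**Step 5. Difference between arms.** With k exits in an arm, all at week 4 (assumption), observed time = (40 − k) × 8 + k × 4.

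| Exits, vitamin C / placebo (assumption) | Vitamin C | Placebo | Ratio, placebo / vitamin C |
|---|---|---|---|
| 6 / 6 | 296 | 296 | 1.00 |
| 4 / 8 | 304 | 288 | 0.95 |
| 3 / 9 | 308 | 284 | 0.92 |
| 0 / 12 | 320 | 272 | 0.85 |

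Equal numbers of exits at the same time leave no imbalance. Even a 3 / 9 split gives a difference of only about 8%.

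**The case against.** The strongest reply is that this is a condensed article. Reporting windows for serious events and contact after withdrawal are usually left to the full protocol, which is not shown. The schedule figure is not available either. That stands as a caution: the full protocol may already cover the gap. It does not remove the point, because the rule in 2.2 is stated, and following it as published ends the scheduled questions at amputation.

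A reader might infer several stronger things that the article does not support:

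- **Adverse events are collected only at visits.** Section 2.9 also gives the 24-hour contact route, and the look-back in 2.10 reaches events between visits.
- **Later serious events will go unrecorded.** The article is silent. What can be said is that no systematic collection is stated.
- **Stopping when consent is withdrawn is a defect.** Collection normally has to stop then.
- **Participants withdrawn for an adverse event or a protocol violation are not followed.** Section 2.12 lists these reasons in order to keep the data in the intention-to-treat analysis. It does not say that visits or contact end.
- **Not substituting adverse event data is an error.** It is normal practice.
- **The 7.5% in the working is the loss from amputation.** It counts all 12 expected withdrawals.
- **The Discussion's statement of minimal side-effect risk depends on these data.** It is a premise, and the Discussion supports tolerability from earlier literature. If fewer vitamin C participants left early, that arm would be observed longer and would tend to show more events, which would not flatter vitamin C.

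It is also fair to say that the amputation itself is recorded, that efficacy for amputation and mortality is declared out of scope, and that the sample size is untouched.

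**Conclusion.** The point holds in a narrow form. Section 2.2 ends participation at amputation, 2.12 treats amputation as a medical withdrawal, and the scheduled safety questions depend on visits that then stop. Serious events and deaths between amputation and week 8 are therefore not systematically collected under the published text.

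The number of participants affected is unknown. About 4% to 11% of participant-weeks is an upper bound that rests on two assumptions: all 12 expected withdrawals end safety observation, and they leave on average between weeks 2 and 6. Unequal observation between arms is a possibility that depends on unbalanced exits, not a demonstrated feature. The share of time lost is modest. However, it includes the weeks straight after amputation, and with 40 per arm serious events are likely to be few, so a few missed ones could alter the comparison. This is a cheap improvement to the safety data; it does not threaten the primary analysis.

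**What to change.** In 2.2, 2.9 and 2.12, state that amputation, or any withdrawal from treatment other than withdrawal of consent to follow-up, does not end safety follow-up. Then:

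- Collect serious adverse events and vital status to the planned week-8 date for every randomised participant, unless consent to that contact has also been withdrawn.
- Where visits have stopped, use a telephone call or a hospital-record check.
- Follow adverse events that are open at exit to resolution or week 8, whichever comes first. This also allows duration to be recorded, as 2.9 intends.

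If the full protocol already says this, a sentence in the article is enough. Otherwise it is a protocol amendment, since section 3.1 reports that recruitment has begun.

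The cost is one or two calls or record checks for at most about 12 expected participants, all recruited through one health service (2.5). The downsides are a little staff time and less detail than a visit gives. Treatment, sample size and the primary analysis do not change.

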### Ethics

2.3

Ethics approval has been obtained from Monash Health Human Research Ethics Committee (RES‐24‐0000‐298A) and the approved project has been noted and accepted by the Deakin University Human Research Ethics Committee (2024‐240). Participants will be informed about the nature of the research, first through discussions with the researchers explaining the study and then through the participant information and consent form. The participant must then provide voluntary written consent to take part in the study. Only after a participant provides informed consent for the study and additional consent for blood collection and storage will they be assessed for eligibility.

### Participants

2.4

Eighty participants will be recruited. The inclusion criteria are adult patients (≥ 18 years old) with either type 1 or type 2 diabetes who present to the high‐risk foot service at multiple sites of Monash Health, Melbourne, Australia, with a foot ulcer. The exclusion criteria are: (i) inability to provide informed consent; (ii) already taking a vitamin C supplement; (iii) already proceeding to amputation following first visit; (iv) haemochromatosis; (v) people on dialysis or proceeding to dialysis following first visit and (vi) injuries arising from prolonged hospitalisation or immobility (i.e., pressure injuries) as these are not typically considered to have the same aetiology as a DFU.

### Recruitment

2.5

Prospective participants will initially be identified by the medical/podiatry team within the high‐risk foot service at Monash Health, which comprises two study sites: Monash Medical Centre and Dandenong Hospital. Prospective participants will then be approached by the research assistant during the patients' scheduled appointment/s at the high‐risk foot service. The research assistant will provide participants with verbal and written information about the study if they indicate that they are interested in participating. The participant will be encouraged to contact the research team if they are interested in participating or alternatively, they will be offered a follow‐up telephone call.

### Randomisation, Concealment and Blinding

2.6

To ensure a similar distribution of wound severity between treatments at baseline, randomisation will be stratified by study site and by ulcer size (≤ 1000 mm^3^ or > 1000 mm^3^) with random block sizes of two and four in a 1:1 ratio. Participants will be centrally randomised to treatment by an independent researcher (known as the randomisation personnel) using a computer‐generated random treatment allocation sequence uploaded onto a secure web platform (REDCap—Research Electronic Data Capture, Vanderbilt University, USA) [29, 30] hosted at Deakin University. The biostatistician on the study team will generate and upload the allocation sequence into REDCap but will have no role in recruitment or data collection. Allocation concealment is facilitated in REDCap by having different user rights and none of the investigators involved in recruitment and data collection or the randomisation personnel will have user rights to access the uploaded allocation sequence. Treatment (placebo and vitamin C) capsules will be in numbered plastic bottles that are otherwise identical. The randomisation personnel will assign numbers to the placebo and vitamin C bottles and only the randomisation personnel will know which treatment is in the numbered bottles. All baseline assessments will be completed prior to treatment allocation.

The randomisation code for an individual participant may only be unblinded in emergency situations, where the Principal Investigator (PI) decides a participant cannot be adequately treated without knowing the identity of their treatment allocation. To break the code, the PI will instruct the randomisation personnel to provide this information directly to the participant's physician/medical team. The time, date, participant code and reason for unblinding will be documented and all members of the research team will remain blinded to treatment during the study.

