#### Ulcer Assessment

2.7.3

Ulcer assessments and measurements will be collected in person by two qualified and experienced (6 and 15 years) Podiatrists at Monash Health who are members of the research team. The number of current ulcers will be recorded. If the participant has more than one ulcer, the largest ulcer will be chosen as the index ulcer [38]. Thereafter, data will only be collected on the index ulcer for this study. Ulcers will then be classified via the Site, Ischaemia, Neuropathy, Bacterial Infection, and Depth (SINBAD) score [39], the WIfI (Wound, Ischaemia, foot Infection) classification [39] and aetiology (neuropathic, ischaemic or neuroischaemic). Ulcer duration and whether the wound is probing to bone, tissue microbiological culture results and any treatment as part of standard care, such as treatment for infection, revascularisation or pressure offloading will be recorded [38]. Amputation outcomes will also be collected, and participants undergoing amputations will be considered not to have healed ulcers.

Ulcer size will be determined by measuring the ulcer length and width with a paper ruler and the depth with a metal probe to calculate the volume in mm^3^. This approach is widely used in a clinical setting [40, 41, 42]. Bedside excisional debridement of nonviable tissue will be conducted prior to wound measurements [28]. Ulcer length will be recorded as the maximum diameter of the ulcer, while ulcer width will be taken as the perpendicular diameter to ulcer length. The ulcer area will be calculated using the ellipse formula [41] and ulcer volume calculated as ulcer area × ulcer depth. A digital image of the wound will also be captured. Interobserver reliability of standard ruler measurements has previously been reported to be excellent for both estimated area (Intraclass correlation coefficients (ICC) 0.98, 95% CI 0.97–0.98) and depth using a probe (ICC 0.93, 95% CI 0.90–0.95) [41]. Also, at the beginning of the study, both Podiatrists underwent the same training according to standard operating procedures for wound measurement that we developed for the trial based on the IWGDF Practical Guidelines (2023 update) [28] and the reliability of wound measurement study by Lasschuit et al. [41].

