### Statistical Analysis

2.15

Primary analyses will be conducted on an intention‐to‐treat basis. Treatment effects for continuous outcomes will be estimated using linear regression models, adjusted for stratification variables study site and baseline ulcer size, and where relevant also baseline level of the outcome. For time‐to‐event outcomes, time to 50% healing and time to complete healing, we will conduct survival analysis, including Kaplan–Meier curves and Cox proportional hazards models (adjusted for study site and baseline ulcer size). Multiple imputation by chained equations will be used to handle missing outcomes data (except for censored time‐to‐event data). Per‐protocol analysis will also be performed on all participants who are > 90% capsule compliant. Complete case analysis will also be conducted to examine if results were sensitive to the approach for handling missing data. Statistical analyses will be conducted using Stata/SE 17.

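### Stratifying by site and one ulcer-volume cut balances only those two factors, and the ulcer duration and SINBAD score recorded at baseline are left out of the planned models, which gives up some precision

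*Protocol article*

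**What the plan says.** All references are to the protocol article.

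- **Aim and method of stratification (2.6).** "To ensure a similar distribution of wound severity between treatments at baseline, randomisation will be stratified by study site and by ulcer size", with the size cut at 1000 mm³, "with random block sizes of two and four in a 1:1 ratio".
- **Eligibility (2.4).** Adults with diabetes "who present to the high‐risk foot service at multiple sites of Monash Health, Melbourne, Australia, with a foot ulcer". No limit on how long the ulcer has been present is given.
- **Recorded ulcer characteristics (2.7.3).** "Ulcers will then be classified via the Site, Ischaemia, Neuropathy, Bacterial Infection, and Depth (SINBAD) score". WIfI class and aetiology are also recorded, as are "Ulcer duration and whether the wound is probing to bone, tissue microbiological culture results". Volume is calculated as area times depth.
- **Background treatment (2.2).** "All participants will continue to receive usual standard of care throughout the trial".
- **Models (2.15).** Linear regressions are "adjusted for stratification variables study site and baseline ulcer size, and where relevant also baseline level of the outcome". The time-to-event outcomes use "Cox proportional hazards models (adjusted for study site and baseline ulcer size").

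**The concern.** Section 2.6 promises comparability on wound severity, but the only severity measure in the stratification is volume, split in two; site does not measure severity. Section 2.7.3 shows that the trial itself regards severity as wider than volume, because it scores ischaemia, infection and neuropathy and records how long the ulcer has been present. Stratification balances the factors it uses. Any other factor is balanced only on average, and in one trial of this size moderate gaps are common.

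Baseline covariates could make up for this in the analysis. Section 2.15 names its covariate set, however, and duration and SINBAD are not in it. This is therefore a criticism of a stated choice, not of detail left to an analysis plan. Both arms receive active standard care for 8 weeks, so part of the change in volume will follow from the condition of the ulcer at entry. If the markers predict that change, leaving them out puts the variation they explain into the residual error.

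**Working it through.** **1. The plan's own figures.** Inputs from 2.14: d = 0.80, two-sided α = 0.05, power 90%, withdrawal 15%.
- The normal approximation gives 33 per arm. The noncentral t gives 34 per arm with power 90.2%, so 68 in total.
- 68 / (1 − 0.15) = 80. Both stated figures reproduce.

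**2. Chance imbalance in a factor unrelated to site and volume.** For a yes/no factor with prevalence p and n per arm, the SD of the difference in proportions is √(2p(1 − p)/n). The documents give no prevalence; 30% to 50% is assumed.

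| n per arm | p | SD of arm difference | Chance of a gap above 15 points |
|---|---|---|---|
| 40 (all randomised) | 0.30 | √(0.42/40) = 0.102 | 14% |
| 40 | 0.50 | √(0.50/40) = 0.112 | 18% |
| 34 (evaluable) | 0.30 | √(0.42/34) = 0.111 | 18% |
| 34 | 0.50 | √(0.50/34) = 0.121 | 22% |

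For a continuous marker, the standardised difference has SD √(2/n). A difference above 0.25 SD has probability 30% at 34 per arm and 26% at 40.

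**3. What an imbalance does to one trial's estimate.** If the marker explains a share R² of outcome variance, an unadjusted imbalance of b SD moves that trial's estimate by b√R². For b = 0.25 and R² from 0.05 to 0.30 (assumed), the shift is 0.25 × 0.224 = 0.06 SD to 0.25 × 0.548 = 0.14 SD, against a planned effect of 0.80 SD.

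**4. Precision gained by adjustment.** The residual SD shrinks by √(1 − R²), so the effective d becomes d/√(1 − R²). Here d is taken as standardised after the adjustments already planned, and R² is what the two markers add. Power at 34 per arm, noncentral t:

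| R² (assumed) | d = 0.80 | d = 0.50 |
|---|---|---|
| 0 (as planned) | 90.2% | 52.9% |
| 0.05 | 91.5% | 54.9% |
| 0.10 | 92.9% | 57.2% |
| 0.20 | 95.3% | 62.2% |
| 0.30 | 97.3% | 68.0% |

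The table keeps 66 degrees of freedom throughout; deducting two for the added covariates lowers no entry by as much as 0.1 percentage points. The d = 0.50 column is illustrative: 2.14 says no SD was available and d was assumed, so a smaller effect is possible.

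**5. Validity without the markers.** In 20,000 simulated trials with no treatment effect, 34 per arm and a marker with R² = 0.20, the unadjusted test rejected in 4.9% of trials. The nominal level holds.

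**6. Events for the Cox models.** Section 2.14 assumes 70% censoring among controls and a hazard ratio of 3.5 for time to 50% healing. The control event share is 0.30, and the treated share is 1 − 0.70^3.5 = 0.713. With 34 per arm, events number 34 × (0.30 + 0.713) ≈ 34. Treatment, site, ulcer size, duration and SINBAD make five parameters, or about 34/5 ≈ 7 events each.

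**The case against.** The strongest reply is that nothing is invalid. Adjusting for the stratification factors, and for the baseline outcome where relevant, is a coherent pre-specified model. Its standard error and type I error already allow for chance imbalance in everything left out. This stands. A reader might infer that an imbalance in ischaemic or long-standing ulcers would bias the trial. The documents do not support that: such an imbalance can move the estimate in one realised trial, but it does not bias the comparison on average.

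Nor do the documents say how well duration or SINBAD predicts 8-week volume change. The predictor they name (2.8.1 and the Discussion) is early percentage change, which neither marker measures. This also stands: the two are baseline severity and chronicity markers and do not capture the ulcer's course before entry. R² is an assumption throughout.

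Volume already carries depth, a SINBAD component, so the two overlap in part. Adding strata in about 80 patients would make cells sparse, so using one severity measure in the randomisation is reasonable. Both points are accepted, and no change to randomisation is proposed.

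The absence of a run-in or an ulcer-age limit might look like a defect. The Discussion says exclusions were kept few so that findings generalise, and a run-in would not by itself balance the arms.

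Finally, further adjusted analyses may sit in an analysis plan that is not shown. That is possible, but 2.15 fixes the covariates of the stated models, and the balance claim in 2.6 is too strong whatever that plan contains.

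**Conclusion.** The point holds as an overstated balance claim and a missed, nearly free gain in precision. Stratification as described balances site and ulcer size only. Neither the design nor the stated models address the other severity and chronicity markers that the trial collects.

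The gain is modest at the planned effect and could be larger if the true effect is smaller. At the assumed R² of 0.05 to 0.30, power rises by 1.3 to 7.1 percentage points at d = 0.80 and by 2.0 to 15.1 points at d = 0.50. Imbalances above 15 points in a factor of 30–50% assumed prevalence would occur in roughly one trial in five to seven. These sizes rest on assumed R² and prevalence. No stated figure is wrong, and the validity of the primary test is not in question.

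**What to change.** 1. **Section 2.6:** state that stratification is meant to balance study site and ulcer size, and drop the claim to ensure balance in wound severity.
2. **Section 2.15, primary linear model:** add log ulcer duration and total SINBAD score, both at baseline, as pre-specified covariates. Fix this in writing before unblinding, because recruitment has begun (3.1) and a later addition could be challenged as data-driven.
3. **Section 2.15, Cox models:** keep site and ulcer size in the main models and add the two markers only in a named sensitivity analysis. Events are few, and added covariates change the conditional hazard ratio being estimated.
4. **Eligibility and randomisation:** leave unchanged.

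The cost is wording plus two degrees of freedom in the linear model. Both variables are already recorded. The partial overlap of SINBAD depth with volume may make the gain smaller than the markers' separate associations with healing would suggest.
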